### Relevant concomitant care permitted or prohibited during the trial {11d}

Use of LPV/r together with medications cleared through cytochrome P450 3A (CYP 3A) can lead to elevated plasma concentrations of the concomitant medication. LPV/r also induces glucuronidation which may affect the exposure of some drugs. Medications that inhibit or induce CYP3A may increase or decrease serum concentrations of LPV/r, respectively. These drug-drug interactions may lead to adverse reactions, loss of therapeutic effect of the concomitant medication, and/or loss of antiviral activity of LPV/r.

Site investigators must therefore review concomitant medications at the time of enrollment. A full list of contraindicated medications appears in the study protocol in Appendix A [37], and the use of any of these products that cannot be substituted during the study dosing period is an exclusion criterion for the study. For other medications and/or supplements that are not on the list of contraindicated medications, site investigators must assess the risk of drug-drug interactions, and adjust medication doses accordingly. Study pharmacists with extensive experience with LPV/r use will provide advice to investigators regarding the management of drug-drug interactions as needed, via email or telephone consultation.

Co-enrollment into other regulated clinical trials of COVID-19 prevention is permitted, but details of the co-intervention must be documented under the concomitant medication section or other suitable part of the database.

### Provisions for post-trial care {30}

This study will provide access to 14 days of the study drug for those randomized to the intervention arm only. Because a secondary objective of the trial is to examine the impact of LPV/r on clinical outcomes in those who test positive for SARS-CoV-2, the full course of study drug should be continued regardless of the results of COVID-19 testing.

In the event that a participant tests positive for SARS-CoV-2 during or after the follow-up period, efforts will be made to link the individual to ongoing clinical trials of COVID-19 treatment. However, no guarantee of access to investigational product can be made. At the time of writing, there are no known effective anti-viral treatments for established COVID-19 infection, although dexamethasone has been shown to improve 28-day mortality in hospitalized patients requiring oxygen or invasive mechanical ventilation [44].

### Outcomes {12}

The primary outcome is microbiologically confirmed SARS-CoV-2 infection, i.e., the proportion of participants with detection of SARS-CoV-2 RNA by polymerase chain reaction (PCR) in a respiratory specimen (oropharyngeal/nasal swab, nasopharyngeal swab, sputum specimen, saliva specimen, oral swab, endotracheal aspirate, bronchoalveolar lavage specimen) by day 14 of the study. This is the most relevant outcome for this PEP trial, since it represents incident SARS-CoV-2 infection. Specimens will be collected on all participants at baseline, day 7, day 14, and within 24 h of new symptoms, as detailed further below.

Secondary outcomes are:
Adverse events: the proportion of participants exhibiting adverse events of any grade as defined using the DAIDS Table for Grading the Severity of Adverse Events, at 7, 14, 35, and 90 days [28].Symptomatic microbiologically confirmed SARS-CoV-2 infection: proportion of participants with fever, cough, or other respiratory/systemic symptoms (including but not limited to fatigue, myalgias, arthralgias, shortness of breath, sore throat, headache, chills, coryza, nausea, vomiting, diarrhea), combined with microbiologic confirmation of SARS-CoV-2 infection by PCR, by day 14.Seropositivity: proportion of participants with reactive serology at day 35.Days of hospitalization attributable to COVID-19 disease: The median number of days (or partial days) spent admitted to an acute care hospital will be tabulated both at day 35 and day 90.Respiratory failure requiring ventilatory support attributable to COVID-19 disease: The median number of days (or partial days) requiring (i) non-invasive or (ii) invasive ventilation will be tabulated both at day 35 and day 90.Mortality (proportion of participants who die) attributable to COVID-19 disease and all-cause mortality will be tabulated at 35 and 90 days.Short-term psychological impact of exposure to COVID-19 will be measured at day 14 using the K10, a validated measure of non-specific psychological distress, with results aggregated as the proportion with a score of ≥ 16 [45, 46].Long-term psychological impact of exposure to COVID-19 will be measured at day 90 using the Impact of Event Scale, a validated measure of traumatic stress response, with results aggregated as the proportion with a score of ≥ 26 [47, 48].Health-related quality of life will be measured using the EQ-5D-5L (EuroQol-5D) (https://euroqol.org/eq-5d-instruments/eq-5d-5l-about/). The EQ-5D consists of two pages: the EQ-5D descriptive system and the EQ visual analog scale (EQ VAS). The descriptive system comprises five dimensions: mobility, self-care, usual activities, pain/discomfort and anxiety/depression. The tool will be administered to participants at 1, 14, 35 and 90 days; the primary interest is in the median index value at 14 days.

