An initial clinical trial in China found no definite treatment benefit of LPV/r in hospitalized COVID-19 patients [9] but was underpowered for the primary endpoint of mortality, and initiation of LPV/r was late in the course of COVID-19 disease. There was also a potential for imbalance in baseline characteristics (higher viral load, later presentation, more severe illness in the LPV/r arm) to influence the outcomes. Secondary endpoints hinted at potential benefit (numerically lower mortality, shorter ICU/hospital stay) [9]. As noted by many observers [10–14], the results underscore the need for more LPV/r trials. While subsequent results from the SOLIDARITY and RECOVERY trials showed no impact of treatment with LPV/r on mortality in hospitalized COVID-19 patients [15, 16], data are lacking on the impact of this drug when used for prophylaxis or pre-emptive therapy.

The safety of LPV/r is already well-established, since it has been widely used in HIV treatment and PEP for over 20 years [17–19]. While it can cause temporary gastrointestinal side effects [20–23], discontinuation due to side effects was uncommon in HIV PEP trials [24–26]. Drug interactions are well understood [27], although the large number of potential interacting agents can pose clinical challenges. LPV/r is safe in pregnancy, liver disease and at all levels of renal function including dialysis and is available in liquid form to facilitate use in children and adults who cannot take pills/tablets [27]. It is also available worldwide, including in resource-limited settings. Thus, the feasibility of LPV/r as COVID-19 PEP is high if shown to be effective, and it is critical to develop evidence regarding its use.

This trial will examine the efficacy and safety of a 14-day course of LPV/r as PEP in close contacts of individuals with confirmed SARS-CoV-2 infection. All items in the WHO trial registry data set can be found in the protocol (Appendix A).

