### Strategies to improve adherence to interventions {11c}

Participants in the active arm of the trial will receive a few doses of dimenhydrinate 50 mg (for management of nausea) and loperamide 2 mg (for diarrhea) in their study kits, in order to help manage potential gastrointestinal side effects of the study drug.

Of note, the study team considered a loading dose of LPV/r at baseline (400/100 mg four times on day 1, followed by twice daily to complete 14 days total) in order to optimize the pharmacokinetics of this drug against SARS-CoV-2. However, this strategy was not selected due to concern that it may be associated with an increased risk of side effects that could compromise further adherence with the study drug.

Adherence will be monitored in two ways. First, participants in the active arm will be asked to complete a daily electronic symptom diary which asks whether each dose was early, on time (within 3 h), late, or forgotten/missed. Second, a random ~ 30% subset of participants in the active arm will have a self-collected dried blood spot collected at day 14 for testing of plasma lopinavir levels as a biomarker of adherence and to assess for a pharmacokinetic correlate of protection. Because these levels can be affected by hematocrit [42, 43], this subset of participants will also undergo a complete blood count at the day 35 in-person visit, together with the routine blood draw for serology.

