^d^An additional swab is to be collected within 24 h if symptoms develop before day 14. Two respiratory specimens (swabs, saliva, etc.) are to be taken at day 14 timepoint, unless an extra swab was already taken due to the development of symptoms in which case only one is collected

*NB:* other respiratory specimen(s) may be collected depending on availability of supplies

^e^The dried blood spot at baseline is to be performed in participants in the active arm only (since these participants are already collecting a drop of blood for the HIV self-test), for SARS-CoV-2 serology

^f^The dried blood spot at day 14 is to be performed in a random subsample of participants in the active arm only, for lopinavir levels. These participants are the only ones that require a CBC at day 35 since the hematocrit is required for interpretation of DBS lopinavir levels [42, 43]

^g^Baseline serology is to be collected at baseline only if the participant is institutionalized

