## Assignment of interventions: blinding

### Who will be blinded {17a}

This trial is open-label at the level of the participant, study coordinator, and investigator due to the impracticality of securing a supply of placebo. However the primary outcome is an objective biological event (microbiologic evidence of virus by RT-PCR), and lab technologists and statisticians will be blinded through the use of a randomly generated secondary participant identification number that is unlinked to cluster.

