## Data collection and management

### Plans for assessment and collection of outcomes {18a}

At baseline, study staff will conduct interviews to capture baseline characteristics of the study sample, including demographics; exposure assessment (relationship with case patient; timing/intensity/frequency of contact; protective measures taken during contact); medical history (comorbidities, medications, smoking) and symptoms.

To obtain specimens for viral RNA testing (primary outcome), participants will be instructed on self-collection of oropharyngeal/nasal swabs as in prior work [64, 65], for RT-PCR testing [66–68]. Specifically, participants are asked to swab the back of their tongue, followed by the throat, before inserting the swab up to 4 cm into each nostril and rotating at least twice. These instructions are also provided in a short instructional video. Specimens will be collected at baseline, day 7, day 14 and within 24 h of new symptoms. In participants who are asymptomatic, a second self-collected swab will also be collected at day 14 and combined in the same specimen vial, or a saliva specimen will be collected if swabs are not available, since having two respiratory specimens tends to increase sensitivity for the detection of respiratory viruses [69, 70]. (If a participant has an earlier swab that is PCR positive then only one swab/saliva specimen needs to be collected at day 14.) Nasopharyngeal swabs and deep respiratory samples (e.g., bronchoalveolar lavage/endotracheal tube aspirates) already done for clinical care purposes will also be collected, with biobanking of specimens not tested in real-time for future analysis.

Follow-up interviews will be conducted at days 7, 14, 35, and 90 to assess for adverse events and clinical outcomes (hospitalizations, mechanical ventilation, mortality). Symptom data will be collected using daily electronic questionnaires that will be emailed daily for days 1–14. Participants will also be provided with a thermometer with which to record their temperature daily on days 1–14.

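### Symptomatic confirmed infection (secondary outcome) can be met by nausea, vomiting or diarrhea alone in a PCR-positive participant; LPV/r can cause these symptoms, so the comparison is biased against it

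*Protocol article*

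**What the plan says.** **Definition.** Outcomes {12} counts fever, cough, or "other respiratory/systemic symptoms (including but not limited to fatigue, myalgias, arthralgias, shortness of breath" and others, the list closing with "headache, chills, coryza, nausea, vomiting, diarrhea), combined with microbiologic confirmation of SARS-CoV-2 infection by PCR", by day 14. It states no minimum number, duration or cause of symptoms.

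**Drug effects.** Background and rationale {6a} says of LPV/r: "While it can cause temporary gastrointestinal side effects". Strategies to improve adherence {11c} supplies the active arm with "dimenhydrinate 50 mg (for management of nausea) and loperamide 2 mg (for diarrhea) in their study kits". The reason given there is tolerability: the medication is provided "in order to help manage potential gastrointestinal side effects of the study drug". The control arm receives no intervention.

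**Ascertainment.** "Symptom data will be collected using daily electronic questionnaires" on days 1–14, which is the dosing period. On blinding {17a}: "This trial is open-label at the level of the participant, study coordinator, and investigator".

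**Analysis.** Statistical methods {20a} compares symptomatic disease between arms with a logit mixed model. It then repeats the secondary outcomes in participants who are PCR-positive at baseline, as the early-treatment analysis. The text shown has no rule that attributes a gastrointestinal symptom to drug or infection.

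**The concern.** Take two infected participants who would have had no symptoms from the virus. The one on LPV/r who develops drug-related diarrhea becomes a case of symptomatic COVID-19. The control becomes one only if an unrelated symptom happens to occur. The outcome then measures tolerability as well as disease, and the error runs in one direction: it raises the event rate on LPV/r.

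In the prophylaxis analysis, the PCR requirement confines the effect to infected participants with no other symptom. In the baseline-positive analysis everyone already meets the PCR criterion, so symptoms alone separate the arms. The Discussion presents early treatment as a question that the trial will explore, so this reading should not be blurred by side effects.

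**Working it through.** **The plan's own figure.** No sample size or power is given for this outcome. The primary figure reproduces: 15% v 9%, two-sided 0.05 (sidedness assumed) and 80% power need 460 per arm. The design effect is 1 + (5 − 1) × 0.05 = 1.2, so 460 × 1.2 / 5 = 110.4 clusters per arm. Then 220 / 0.9 = 244.4 rings, and 244 × 5 = 1220. The concern does not touch this figure.

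**Model for the bias.** Let *a* be the share of infections with no symptom from the infection, and *g* the rate of drug-caused gastrointestinal symptoms on LPV/r. Neither is in the documents; both are assumptions. With no background gastrointestinal symptoms in controls:

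observed RR = true RR × [(1 − a) + a·g] / (1 − a)

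| a | g | factor | RR seen if true RR = 1.00 | RR seen if true RR = 0.60 |
|---|---|---|---|---|
| 0.20 | 0.20 | 0.84 / 0.80 | 1.05 | 0.63 |
| 0.20 | 0.60 | 0.92 / 0.80 | 1.15 | 0.69 |
| 0.40 | 0.20 | 0.68 / 0.60 | 1.13 | 0.68 |
| 0.40 | 0.40 | 0.76 / 0.60 | 1.27 | 0.76 |
| 0.40 | 0.60 | 0.84 / 0.60 | 1.40 | 0.84 |

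**Background symptoms in controls.** If a share *b* of otherwise asymptomatic infected controls also report such symptoms, and *g* is the total rate on LPV/r, the denominator becomes (1 − a) + a·b. At b = 0.10 the two extreme rows fall to 0.84 / 0.82 = 1.02 and 0.84 / 0.64 = 1.31. At a = 0.35 and g = 0.30, the null ratio is 0.755 / 0.65 = 1.16 with no background, 1.13 at b = 0.05 and 1.10 at b = 0.10.

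**Baseline-positive analysis.** At a = 0.35 and g = 0.30, an ineffective drug gives 65% symptomatic in controls and 0.65 + 0.35 × 0.30 = 75.5% on LPV/r. The risk ratio is 1.16. The planned logit model reports odds ratios, and the marginal odds ratio is (0.755 / 0.245) / (0.65 / 0.35) = 1.66.

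**Power for the secondary outcome, same illustration.** The effective size is 550 / 1.2 = 458 per arm, and the control risk is 0.15 × 0.65 = 0.0975. With a true RR of 0.60, the LPV/r risk is 0.0585 without the bias (power about 60%) and 0.15 × 0.60 × 0.755 = 0.068 with it (power about 37%).

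**With the fix.** Setting g = 0 returns the observed ratio to the true one, 1.00 or 0.60.

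**The case against.** **The PCR requirement limits the effect.** Gastrointestinal side effects alone never make a case, and the list is broad enough that many infected participants will qualify on another symptom. This stands. It is why the size depends on the otherwise asymptomatic share.

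**The figures are assumed.** Both rates come from outside the documents, and the upper end needs both extremes together. The supplied medication may also offset part of the effect. This stands, so the figures are illustrative.

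**The trial could hardly detect it.** At a = 0.35 and g = 0.30, with 1220 × 0.9 / 2 = 549 evaluable per arm, there are 549 × 0.0975 ≈ 54 control events and 549 × 0.15 × 0.755 ≈ 62 on LPV/r. That is a ratio of 1.16 with a 95% interval of roughly 0.8 to 1.7 (design effect 1.2). So it goes too far to say that a useless drug would look harmful. The bias also cannot produce a false claim of benefit. It can still hide or dilute a real one.

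**The analysis plan may deal with it.** A sensitivity analysis is commonly left to that document, and the full protocol is not shown either. But the definition is fixed in this article, and the definition is the problem. Adverse events are assessed for relatedness {22}, but in the investigational arm only and with no link to this outcome.

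**Readings that go further than the text.** A reader might blame the open-label design. The mechanism is pharmacological and would operate under blinding too; open-label reporting could only add to it. A reader might also say that the plan names vomiting as a side effect. It names nausea and diarrhea, and vomiting falls only under the general gastrointestinal wording.

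Finally, a reader might infer that the primary outcome is biased through symptom-triggered testing, since Table 1 footnote d says "An additional swab is to be collected within" 24 hours when symptoms appear before day 14. The documents do not support that step. They do not list which symptoms trigger the swab, and footnote d lets the extra swab replace the second day-14 specimen. An early swab might precede detectable virus as easily as catch it. Neither direction nor size is shown.

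**Conclusion.** The concern holds for the secondary outcome of symptomatic confirmed infection, in the prophylaxis analysis and more directly in the baseline-positive analysis. As defined, drug-caused gastrointestinal symptoms in infected participants with no other symptom push the risk ratio upward, against LPV/r.

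The illustrative size is 1.05 to 1.40 under no effect, and 0.63 to 0.84 for a true 0.60. This assumes 20–40% otherwise asymptomatic infections, 20–60% drug-caused symptoms and no background symptoms in controls; with background symptoms it is smaller. The primary outcome rests on PCR alone, and its definition and sample size are unaffected.

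**What to change.** **Preferred.** For the between-arm comparisons in both the prophylaxis and baseline-positive analyses, define symptomatic infection as PCR confirmation plus at least one non-gastrointestinal symptom, and report the current definition alongside.

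**Minimum.** Keep the current definition and pre-specify a sensitivity analysis that sets aside participants who qualify on nausea, vomiting or diarrhea alone. Count them as non-events and keep them in the denominator. Dropping them would leave bias in the baseline-positive set: at a = 0.35 and g = 0.30, 0.65 / (1 − 0.105) = 72.6% v 65%, a ratio of 1.12 under no effect.

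**Cost.** Wording and a further tabulation from symptom diaries already collected. True gastrointestinal-only infections go uncounted, by the same rule in both arms; the documents do not say how many there would be. Recruitment opened in April 2020, so a redefinition should be dated and justified before comparative data are examined. The minimum option avoids redefining the outcome.

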## Statistical methods

### Statistical methods for primary and secondary outcomes {20a}

The primary outcome is microbiologically confirmed SARS-CoV-2 infection, i.e., detection of viral RNA in a respiratory specimen (oropharyngeal/nasal swab, nasopharyngeal swab, sputum specimen, saliva specimen, oral swab, endotracheal aspirate, bronchoalveolar lavage specimen) by day 14. Our primary analysis will be a generalized linear mixed model (GLMM) with logit link to estimate the effect of LPV/r on the probability of infection while accounting for clustering of participants in rings, with stratification by the randomizing site. The primary analysis will be unadjusted; in addition, multivariable models will adjust for key characteristics of both contacts (age, sex, co-morbidity, exposure characteristics such as type, duration, and timing) and index cases (illness severity, concomitant medications, etc.). In particular, we will include sex/gender-based analyses with variables specific to contacts and types of exposures. Participants with specimens positive for SARS-CoV-2 at baseline will be permitted to continue in the trial and follow all study procedures, including completion of the 14-day course of study drug for those in the active arm, as noted in section 12.2.2. These participants will be excluded from the primary and secondary analyses regarding LPV/r as PEP, but included in secondary analyses regarding early LPV/r treatment, as noted below.

To assess safety, adverse events will be tabulated according to grade and causality assessment using definitions from the DAIDS Table for Grading the Severity of Adverse Events [28], and compared between study arms.

As for the primary analysis outlined above, GLMM with logit link (for dichotomous outcomes) or identity link (for continuous outcomes) will also be used to compare the following secondary outcomes between study arms:

Symptomatic COVID-19 disease by day 14Seropositivity by day 35Days of hospitalization attributable to COVID-19 disease by day 90Respiratory failure attributable to COVID-19 disease requiring (i) non-invasive and (ii) invasive ventilation by day 90Mortality attributable to COVID-19 diseaseShort-term psychological distress, defined as scoring ≥ 16 on the K10 [45, 46] at day 14Long-term traumatic stress response, defined as scoring ≥ 26 on the IES scale [47, 48] at day 90Health-related quality of life, measured by the EQ-5D-5 L on days 1, 14, 35, and 90

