Additional secondary analyses will examine the role of LPV/r in early treatment of COVID-19, in the subset of participants whose baseline specimens test positive for SARS-CoV-2. GLMM models will be used to compare the same secondary outcome measures described above.

Key transmission-related epidemiologic parameters among exposed contacts including exposure histories, cluster size, secondary attack rate (p_0_, incidence proportion), time to first viral shedding will be analyzed using descriptive statistics. Risk factors for transmission and correlates of symptomatic disease will be analyzed using logistic regression models.

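### Hospitalisation and ventilation are defined as median days, which will be zero in both arms of the prophylaxis comparison; the model for hospital days estimates a mean difference instead, and the form of the ventilation outcome is unclear

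*Protocol article*

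**What the plan says.** Objectives {7} lists hospitalisation and respiratory failure requiring ventilation as events to be compared between arms.

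Outcomes {12} turns both into durations. For hospitalisation: "The median number of days (or partial days) spent admitted to an acute care hospital will be tabulated", at day 35 and again at day 90. For respiratory failure: "The median number of days (or partial days) requiring (i) non-invasive or (ii) invasive ventilation will be tabulated both at day 35 and day 90". Neither definition is limited to participants who were admitted or ventilated. In the same list, adverse events, symptomatic infection, seropositivity, mortality and the two psychological outcomes are defined as proportions.

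Statistical methods {20a} says: "GLMM with logit link (for dichotomous outcomes) or identity link (for continuous outcomes) will also be used to compare the following secondary outcomes". Its list names days of hospitalisation by day 90, but for ventilation it names respiratory failure requiring support by day 90, with no mention of days. Of participants positive at baseline it says: "These participants will be excluded from the primary and secondary analyses regarding LPV/r as PEP". For the early-treatment comparison in that subset: "GLMM models will be used to compare the same secondary outcome measures described above".

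**The concern.** Only infected participants can accumulate COVID-19-attributable days, and the prophylaxis population consists of community contacts who test negative at baseline. A median over all of them is zero in each arm unless at least half of the arm has an attributable day, so the defined summary says nothing about the drug.

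The model does not repair this. An identity link targets the difference in mean days, a different quantity from the median, and one that depends on how many people are admitted and how long the few stays last. For ventilation the reader cannot tell whether days or a yes/no event will be modelled. Two clinically important secondary outcomes could then be reported as 0 versus 0 beside an unstable mean difference. The primary outcome and the sample size are not affected.

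**Working it through.** **Inputs from the article (Sample size {14}, Abstract).** Attack rate 15%; relative reduction 40%, so 15% × 0.6 = 9% under LPV/r; 5 contacts per ring; ICC 0.05; 80% power; alpha 0.05; 110 clusters per arm before a 10% loss allowance; 1220 participants.

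**Reproducing the plan's figure.** Unpooled two-proportion formula, two-sided: 456.5 per arm. Design effect 1 + (5 − 1) × 0.05 = 1.2. Clusters per arm: 456.5 × 1.2 / 5 = 109.6, so 110. Loss allowance: 220 / 0.9 = 244.4 rings and 1100 / 0.9 = 1222 people. This matches the stated 244 and 1220. Evaluable per arm: 1220 × 0.9 / 2 = 549. Baseline positives are not subtracted because their number is not given, so the counts below are, if anything, high.

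**Is the median zero?** Expected infections are 549 × 0.15 = 82 (control) and 549 × 0.09 = 49 (LPV/r). Take the extreme case in which every infected person is admitted. The binomial probability that at least half of 549 have any day is about 5e-82 at a 15% attack rate and about 1e-22 at 30%. These figures ignore clustering, but a simulation with ICC 0.05 and 109 rings of 5 per arm also gave a zero median at every admission rate tried. The highest cited household rate is 19.3% (interval to 23.9%); the widest cited interval, from 19 contacts, reaches 31.4%. The attack rate is a day-14 figure while days are counted to day 90, but later infections would not plausibly put half of an arm in hospital. No admission rate is needed for this result, and it applies equally to ventilation days.

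**What does the mean difference rest on?** The article gives no admission rate, so a range is assumed. Expected admissions = 549 × attack rate × share admitted. The last two columns come from 4000 simulated trials with assumed log-normal stays (median 7 days, log-SD 1).

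| Infected who are admitted (assumed) | Admissions, control | Admissions, LPV/r | Share of all days in the two longest stays (median) | Trials where setting those two stays to zero reverses or nullifies the difference |
|---|---|---|---|---|
| 1% | 0.8 | 0.5 | 100% | 89% |
| 2% | 1.6 | 1.0 | 96% | 68% |
| 5% | 4.1 | 2.5 | 63% | 36% |
| 10% | 8.2 | 4.9 | 43% | 26% |
| 20% | 16.5 | 9.9 | 29% | 19% |

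With less skewed stays (log-SD 0.6), the two longest hold 100%, 51% and 31% of days at 2%, 5% and 10% admitted. If 10-30% of those admitted are ventilated (also assumed), at most about 2.5 ventilated controls are expected for admission rates up to 10%.

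**What would a proportion give?** At 5% admitted: 0.15 × 0.05 = 0.75% versus 0.09 × 0.05 = 0.45%. The standard error is √[(0.0075 × 0.9925 + 0.0045 × 0.9955) / 549] = 0.0047, so z = 0.0030 / 0.0047 = 0.64 and power is about 9%. At 10% admitted: 1.5% versus 0.9%, standard error 0.0066, z = 0.91, power about 15%. With the design effect of 1.2 the powers are 8.5% and 13%.

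**The case against.** The best defence is that the median is only a tabulated summary and that the comparison itself is the model, whose mean difference is not fixed at zero. That is correct. A reader might infer that these outcomes cannot show benefit or harm at all, and the article does not support that. Sparse events limit any analysis: simulated power for days versus any admission was 5% versus 8%, 10% versus 13% and 16% versus 24% at 5%, 10% and 20% admitted.

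Other stronger readings also fail:

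- **Invalid standard errors.** Section {20a} names a link, not an error distribution. In null simulations, a t-test on ring means, equivalent to the balanced random-intercept test, rejected in 0.6-1.2% at 2% admitted, 2.4-3.6% at 5%, 3.8-4.3% at 10% and 3.9-4.5% at 20%. That is conservative to near nominal, with no excess of false positives.
- **One or two long stays decide the result.** This needs an admission rate and stay lengths that the article does not give. It fits at 1-2% admitted and largely at 5%; at 10-20% a handful of stays matter.
- **Ventilation goes to the identity link.** Section {20a} does not say so. A yes/no outcome with logit link is an open reading.
- **15% as a ceiling.** It is a planning value; cited household rates include 16.3% and 19.3%.
- **Death is hidden in the day counts.** Attributable and all-cause mortality are tabulated separately at days 35 and 90.
- **The zero median carries over to early treatment.** Everyone in that subset is infected, so a zero median there requires that fewer than half are admitted.

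The sponsor may have meant the median among those admitted. The text does not say this, and it would condition on an event after randomisation.

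**Conclusion.** The point holds in a limited form, and it is wrong as written rather than merely left to an analysis plan. In the prophylaxis population the defined medians are 0 versus 0 at the planning attack rate and at every cited one, without any assumption about admission. The model for hospital days targets a mean and so does not estimate the defined quantity. Sections {12} and {20a} disagree on, or leave open, the form of the ventilation outcome. The instability of the mean difference is conditional: at an assumed 1-10% admitted, it rests on roughly 1-8 control and 0.5-5 LPV/r admissions. The consequence is confined to secondary outcomes.

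**What to change.** In Outcomes {12} and Statistical methods {20a}, define each outcome as a proportion by day 35 and by day 90: any COVID-19-attributable hospitalisation, any non-invasive ventilation, and any invasive ventilation. This restores agreement with Objectives {7}. Compare arms by a risk difference with an interval that respects rings, using a ring-level permutation or exact method if events are few. Report days only in support, for example as hospital-free and ventilator-free days to day 90 with death set to 0. Use the same definitions in the baseline-positive subset.

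The cost is wording only: section {18a} already collects hospitalisation, mechanical ventilation and mortality at each follow-up interview. The downside is that power stays at about 9-15% if 5-10% of infected participants are admitted, so the comparison should be presented as an estimate and not as a test likely to be conclusive.
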